### **7.3.4 Diabetic ketoacidosis (DKA)**

The National Evidence-Based Clinical Care Guidelines for Type 1 Diabetes in Children, Adolescents and Adults (2011) [1] states “DKA is life-threatening acute complication of type 1 diabetes. It occurs when insulin delivery is insufficient to prevent progressive hyperglycaemia and ketone body formation. Like hypoglycaemia, DKA can occur in anyone with type 1 diabetes, but is more common when there is a precipitant (e.g., infection of the gastrointestinal, respiratory or urinary tract). Aiding self-care, adherence to therapy and ‘sick day’ management can prevent many cases

of threatened or mild DKA from worsening and requiring hospitalisation.” DKA is a medical emergency that should only be treated in hospital. Steps taken in this study are aimed at *preventing* the development of DKA in participants. If any participant at any time-point throughout the study is experiencing symptoms of ketoacidosis, they should dial 000 or present to emergency immediately.

Given that participants in this study must have been diagnosed with T1D and receiving insulin therapy for at least six months, the risk of any participant developing DKA would most likely be associated with inappropriate sick day management or cessation of insulin therapy. To mitigate the risk of DKA, participants will receive ongoing support from a member of their usual diabetes team (an endocrinologist, a diabetes educator or a general practitioner) for all matters related to insulin therapy and general diabetes management, including the prevention of DKA. In addition, participants and their nominated HCP will receive an information pack at the start of the study which will include the resources, ‘Managing sick days’ (Attachments 43 and 46), which provide information on DKA and how to monitor for and prevent DKA when participants are feeling unwell.

For safety purposes, participants will be required to self-monitor either urine or blood ketones regularly throughout the intervention period using their usual method(s) of measuring ketones. Participants will be required to measure their ketones at least twice per week, and more under certain circumstances (e.g., if feeling unwell) as per standard of care diabetes practices. To assist participants in doing this, the required amount of ketone test strips will be provided. A resource titled, ‘Self-monitoring ketones’ (Attachment 52) will be provided at the beginning of the intervention period to instruct participants on how and when to monitor for ketones, what level of ketones are and are not expected, and what to do if they are experiencing unexpected changes in blood or urine ketones. The resource will help participants understand that mild, controlled ketone readings are normal and expected with the LC dietary intervention. Nutritional ketosis is typically defined as a ketone reading within the range of 0.5–3.0 mmol/L [23] and should not be confused with DKA that is associated with a rapid increase in ketone levels typically 10 times the level observed with nutritional ketosis. Nevertheless, we are taking a conservative approach and advising participants to maintain ketones  $\leq 0.6$  mmol/L, as per usual standard diabetes practice. The resource, ‘Self-monitoring ketones’ (Attachment 52), includes guidelines on when to monitor for ketones, and what action to take if ketones are  $>0.6$  mmol/L. In brief, participants will

be advised to refer to the resource titled 'Managing sick days' (Attachment 43) for more information. In any case, participants will be instructed to immediately inform [name] (study dietitian) of any instances where ketones are  $>0.6$  mmol/L and the case will be flagged with the study endocrinologist. The overseeing endocrinologist will then make a decision to either (a) continue as is or under certain condition (e.g., need to monitor ketones once daily); (b) refer them to their nominated HCP or GP for independent review; or (c) refer them to the study diabetes educator or study physician for review. If [name] is unavailable, then [name] will be consulted to review the case. All cases referred will be documented and used to assess safety of the intervention in the data analysis and reporting.

### **7.3.5 Psychological or emotional stress**

Any change(s) in chronic disease management, including an increased awareness of disease state (e.g., increased frequency of blood glucose monitoring), can be psychologically demanding and/or emotionally distressing. Health assessments included as part of the study may also bring up underlying psychological/emotional issues (e.g., emotional relationships with food). At the onset of the study (start of control period, Table 1), participants will be provided with an NDSS fact sheet relating to diabetes distress which includes contact details for free counselling/support services that participants can access at any time during or after the study (<https://www.ndss.com.au/wp-content/uploads/fact-sheets/fact-sheet-diabetes-distress.pdf>). Participants will also be provided opportunity to discuss any issues they may be experiencing with the study dietitian during regular diet consults. The dietitian will flag any psychological issues or emotional stress with the study physician or the participants' nominated HCP and/or GP who may then refer participants to the appropriate health professional service for management.

### **7.3.6 Social distress**

There is also a risk of social distress with increased travel and time commitments associated with participation in the study given participants will need to attend several study visits, diet sessions and pathology collection centres. To reduce the burden on participants, diet sessions 2-5 have been organised as Telehealth consults (via Zoom video conference) and there is opportunity to complete all study sessions remotely, if required or preferred. Sessions will be scheduled at a time of day that is most suitable

for the participants (including weekends and outside of working hours if necessary, to not affect participants' usual routines).

## **8. SAFETY CONSIDERATIONS**

### **8.1 Adverse event definitions**

For the purposes of this study, we will define adverse events as any incident that results in the participant requiring health care of which is directly attributed to involvement in the study. The expected risk of serious adverse events experienced as a result of the dietary intervention is low. However, participants will be advised to report details of any adverse events directly to the study dietitian or physician at any point during the control or intervention periods. In the unexpected case of a medical emergency, participants will be encouraged to dial 000 immediately and follow-up with researchers after medical treatment/assessment has been received and their condition is stable.

Adverse events have been described in detail in section 7.3 as potential risks that may be involved with participation in this research and include;

- Discomfort or infection(s) at the site of CGM/FGM, finger prick or venepuncture
- Increased frequency of hypoglycaemia
- Dehydration or sodium deficiency (e.g., headaches, muscle cramps, low energy, digestive discomfort)
- Diabetic ketoacidosis
- Psychological/emotional distress
- Social distress

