review their dietary carbohydrate prescriptions with the dietitian. Blood glucose targets will be consistent with standard practice diabetes targets and are:

- 4-8 mmol/L when fasting and before meals
- 4-10 mmol/L two hours after starting meals

Participants will be encouraged to share their glucose data with the study dietitian, either via their glucose monitoring software online or by downloading their glucose data from their glucose-monitoring device (which stores the blood glucose data) and providing it to the study dietitian via email or Zoom conferencing for discussion/review. This data will be used for monitoring purposes only and will not be used for the formal outcome analysis.

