### 7.3.2 Hypoglycaemia

Hypoglycaemia is a common acute complication of T1D which generally results from the difficulties in predicting expected rises in blood glucoses levels and accurately calculating insulin requirements. Due to the expected change(s) in insulin requirements as a result of the diet intervention, there is a risk of participants miscalculating their insulin requirements in the early stage of the intervention which could lead to increased frequency and/or severity of hypoglycemia. This will be mitigated by close monitoring of blood glucose levels, regular contact with the study dietitian, ongoing support from a nominated HCP, and oversight/supervision by the study physician, study diabetes educator and study endocrinologist.

Hypoglycaemia is defined by Diabetes Australia as a blood glucose level below 4 mmol/L [27]. The resources developed by the study dietitian and diabetes educator titled 'Managing hypoglycaemia' (Attachments 42 and 48) provide participants with information and guidelines on preventing and/or managing hypoglycaemia during the study. Participants will be required to test their blood glucose levels at least six times every day (i.e., before and 2 hours after each meal) using their own glucose monitoring

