device, as per standard of care diabetes practice. They will also be encouraged to test their blood glucose levels before going to bed and before driving or participating in exercise. Participants will also be advised to test their glucose more often if they are: feeling sick or stressed; more or less physically active; experiencing more hypos than usual; experiencing changes in their routine; experiencing night sweats or morning headaches; noticing frequent instances of high blood glucose levels; and/or starting on new medications. Participants will be asked to provide their blood glucose data from their blood glucose monitoring device to the dietitian for review every fortnight throughout the study. If using a CGM or flash glucose monitor (FGM), any reading(s)  $<4$  mmol/L should be confirmed with a finger prick device. If two or more readings across a 14-day period are  $<4.0$  mmol/L then the dietitian will flag the case with the study endocrinologist. The overseeing endocrinologist will then make a decision to either (a) continue until the next review (14 days); (b) refer them to their nominated HCP or GP for independent review; or (c) refer them to the study diabetes educator or study physician for review. If [name] is unavailable, then [name] will be consulted to review the case. All cases referred will be documented and used to assess safety of the intervention in the data analysis and reporting. Participants with hypo unawareness will be excluded from participating in the study. However, if any participant believes they might have developed hypo unawareness during the study, they will be advised to contact [name] (study dietitian) as soon as possible, who will flag the case with the study endocrinologist to be assessed on an individual basis.

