### **8.2 Assessment and documentation of adverse events**

We will use the University of Sydney's non-clinical trials adverse events reporting form as this is the most appropriate form for our study. All adverse events will be documented by [name] as soon as notification about the event is received. [name] will notify the study physician immediately who will assess the situation and make a decision as to what action is required to prevent recurrence of the event (e.g., changing the design of the study, stopping the study, making changes to the participant information sheet, etc.).

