### 9.2 Secondary outcomes

- Glycaemic variability (GV) markers (including Standard Deviation (SD) intraday and mean amplitude of glycaemic excursions (MAGE) [derived from 7-day CGM/FGM data]
- Frequency of hypoglycaemia (<3.5 mmol/L with or without symptoms) [derived from 7-day CGM/FGM data]
- Total daily insulin (TDI) [the sum of all long-acting and rapid-acting insulin given over a 24-hour period derived from a 3-day self-report insulin log]
- Quality of life [measured using the 15-item DQOL Brief Clinical Inventory [25]]

GV markers have been identified as independent risk factors for diabetes complications including CVD, underscoring the importance of this assessment to more rigorously evaluate the effect(s) of the diet intervention on diabetes management.

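### Section 8.1 counts an adverse event only if it needs health care and is already attributed to the study, which conflicts with its own list and with the Table 1 prompts

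*Protocol*

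**What the plan says.** **Definition and list (section 8.1).** An adverse event is "any incident that results in the participant requiring health care of which is directly attributed to involvement in the study". The same section then lists what adverse events include: discomfort or infection at a sensor or needle site, "Increased frequency of hypoglycaemia", "Dehydration or sodium deficiency (e.g., headaches, muscle cramps, low energy, digestive discomfort"), ketoacidosis, and psychological and social distress. Reporting covers the control and intervention periods.

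**Handling (section 8.2).** Adverse events go on a university form. The team member who documents one "will notify the study physician immediately who will assess the situation and make a decision as to what action is required".

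**Prompts (Table 1).** Diet sessions 2 and 3 ask about adverse events, with hypoglycaemia below 3.5 mmol/L among the examples. Session 4 uses the same example but asks about side effects. Sessions 5 and 6 return to adverse events but name severe hypoglycaemia instead.

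**Separate glucose route (section 7.3.2).** Participants are asked to hand over home glucose data every fortnight. With two or more readings below 4.0 mmol/L in 14 days, "then the dietitian will flag the case with the study endocrinologist". The endocrinologist then chooses (a) to carry on to the next review, (b) to refer to the usual practitioner, or (c) to refer to the study educator or physician. Referred cases are documented and used in the safety assessment. Sections 6.6.3 and 7.3.4 use a parallel scheme for ketones.

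**Outcome measurement (section 9.2).** The secondary outcome is "Frequency of hypoglycaemia (<3.5 mmol/L with or without symptoms) [derived from 7-day CGM/FGM data"), measured before the control period, after it, and at the end of the intervention.

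**The concern.** A definition of adverse event decides what is collected. If the entry rule is too narrow, no later analysis can recover what was left out. Three features make this rule matter here.

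- It has two entry conditions. A low that the participant treats with food fails the health-care condition. An event whose cause is not yet known fails the attribution condition. Section 8.1 does not say who judges attribution, and under section 8.2 the physician sees only what already counts as an adverse event.
- The study has no concurrent arm, and the Synopsis says that the dietitian who delivers the diet also collects and analyses the data, unblinded. Relatedness is best judged after recording, by someone other than the person delivering the diet.
- The protocol expects the extra harm early. Section 7.3.2 says "there is a risk of participants miscalculating their insulin requirements in the early stage of the intervention which could lead to increased frequency". Outcome sensor data on the diet are collected only in its last week, and section 6.6.2 says of the shared home glucose data: "This data will be used for monitoring purposes only and will not be used for the formal outcome analysis". What is known about the early weeks therefore leans on safety records, and those records need a consistent rule.

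**Working it through.** **Step 1. Apply each text to the same event.**

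| Event during the diet | 8.1 definition | 8.1 list | Table 1 prompt | Other route |
|---|---|---|---|---|
| Single self-treated low below 3.5 mmol/L in a fortnight | Out: no health care | Only if lows become more frequent | Named at sessions 2-4; not named at 5-6 unless severe | No 7.3.2 flag if it is the only reading below 4.0 mmol/L in 14 days |
| Repeated self-treated lows | Out: no health care | In, if more frequent than usual | As above | 7.3.2 flag to the endocrinologist |
| Mild headache or low energy | Out: no health care | In | Named at sessions 2-6 | 7.3.3 symptom check each fortnight; physician only if severe |
| Social distress | Out unless care is needed | In | Not named | None stated |
| Health-care visit, cause not yet judged | Out until attributed | Depends on the event | Open question about adverse events (sessions 2, 3, 5 and 6) | None stated, unless a glucose, ketone or sodium rule applies |

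Staff cannot follow both the defining sentence and the list. Where they differ, the sentence is always the narrower.

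**Step 2. What the outcome sensor covers.** The intervention runs from the end of week 4 to the end of week 16.

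- Diet period: 16 − 4 = 12 weeks = 12 × 7 = 84 days. This reproduces the stated 12 weeks.
- Outcome CGM/FGM on the diet: week 16 only = 7 days.
- Covered: 7/84 = 8.3%. Not covered: 77/84 = 91.7%, or 11 of 12 weeks.

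This is the coverage of one instrument. It does not count events lost, and no adverse-event wording would change it.

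**Step 3. What the 7.3.2 flag can miss.** The flag needs at least two readings below 4.0 mmol/L in 14 days, so one reading per fortnight never triggers it. Over the diet period, 84/14 = 6, so up to 6 such readings per participant could stay below the threshold. This is a ceiling on readings, not an expected number. A low that is measured twice would itself reach the threshold.

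**Step 4. Which flags are documented.** Options (b) and (c) are worded as referrals; option (a) is not. The documentation sentence covers referred cases. If it means cases referred under (b) or (c), flags closed under (a) are left out. If it means cases passed up to the endocrinologist, they are included. The text does not settle this, and the ketone sections have the same ambiguity.

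**Step 5. Size.** The protocol states no hypoglycaemia rate, so the number of events that would be misclassified cannot be calculated.

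**The case against.** The strongest reply is that lows are recorded elsewhere. Section 7.3.2 requires at least six glucose tests a day and a fortnightly review. Its flag needs neither health care nor attribution, and referred cases enter the safety analysis. Section 10.1 lists glucose logs among the collected data and sends all collected data to REDCap. Section 6.6.2 bars the home data from the formal outcome analysis, not from safety reporting. The prompts at sessions 2 to 4, where the risk is expected, all name the 3.5 mmol/L level, and every prompt offers examples, not cut-offs.

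Most of this stands, and it rules out three stronger readings.

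- A reader might infer that self-treated lows go unrecorded in 11 of the 12 diet weeks. The documents do not support that: the 11 weeks describe sensor coverage, and repeated lows have their own path. One caveat remains, since section 6.6.2 only encourages participants to share their data.
- A reader might infer that on-diet hypoglycaemia has no usual rate for comparison. Week 0 and week 4 CGM/FGM supply one, and the glucose review runs throughout the study. The point holds only for adverse-event reports, where requiring attribution tends to exclude background events in the control period.
- A reader might infer that sending glucose flags to the endocrinologist contradicts sending adverse events to the physician. Both can happen, and section 7.3.3 has a similar split for sodium symptoms. This is an overlap that the protocol does not resolve.

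The reply does not remove the mismatch in section 8.1 or the attribution test at entry.

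**Conclusion.** The point holds as a fault of classification and capture. The defining sentence in section 8.1 conflicts with its own list and with the Table 1 prompts, and those prompts change wording during the diet. Applied literally, it keeps self-treated lows and mild symptoms out of the recorded adverse events and settles attribution before any medical assessment. The unclear treatment of flags closed under option (a) is a smaller, related ambiguity.

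The conclusion assumes that staff apply the defining sentence as written. If they work from the list instead, most of these events are recorded, but nothing in the text tells them to. The change should be made, but no estimate of lost events can be attached to it.

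**What to change.** - **Section 8.1:** record every untoward event in the control and intervention periods, whatever its cause or need for care. Have the study physician judge relatedness afterwards.
- **Table 1:** use one hypoglycaemia wording, below 3.5 mmol/L to match the secondary outcome, and the term adverse event at every prompted session.
- **Sections 6.6.3, 7.3.2 and 7.3.4:** state that every hypoglycaemia and ketone flag is documented for the safety analysis, including those resolved under option (a).
- **Section 8.2:** keep immediate physician notice for serious or care-requiring events and review the rest periodically. Without this change, a wider definition would send every minor headache and self-treated low to the physician at once.

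The cost is a short amendment, more adverse-event forms, and some extra review by a physician who gives time in kind, for about 20 participants. It needs no new visits, devices or staff.

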### **8.2 Assessment and documentation of adverse events**

We will use the University of Sydney's non-clinical trials adverse events reporting form as this is the most appropriate form for our study. All adverse events will be documented by [name] as soon as notification about the event is received. [name] will notify the study physician immediately who will assess the situation and make a decision as to what action is required to prevent recurrence of the event (e.g., changing the design of the study, stopping the study, making changes to the participant information sheet, etc.).

## 9. OUTCOMES

All primary, secondary and additional outcomes will be measured at three time-points: (1) pre-control period, (2) post-control period / pre-intervention period, and (3) post-intervention period. The only data being collected at follow up (12 weeks post-intervention) is HbA1c, total daily insulin (previous 24 hours), dietary intake (previous 24 hours), diabetes-related quality of life and diet satisfaction. Refer to Table 1 for a clear description of what outcomes are being measured at what time-points throughout the duration of the study for each participant. Refer to Figure 1 for an overview of this information.

### 9.1 Primary outcome

- Haemoglobin A1c, HbA1c (% and mmol/mol)\*

### 9.2 Secondary outcomes

- Glycaemic variability (GV) markers (including Standard Deviation (SD) intraday and mean amplitude of glycaemic excursions (MAGE) [derived from 7-day CGM/FGM data]
- Frequency of hypoglycaemia (<3.5 mmol/L with or without symptoms) [derived from 7-day CGM/FGM data]
- Total daily insulin (TDI) [the sum of all long-acting and rapid-acting insulin given over a 24-hour period derived from a 3-day self-report insulin log]
- Quality of life [measured using the 15-item DQOL Brief Clinical Inventory [25]]

GV markers have been identified as independent risk factors for diabetes complications including CVD, underscoring the importance of this assessment to more rigorously evaluate the effect(s) of the diet intervention on diabetes management.

### 9.3 Additional outcomes

- Body Mass Index (BMI) (kg/m^2) [height and weight measured using standard procedures by study dietitian^]
- Waist circumference (cm) [measured at the midline point between the lowest rib and iliac crest by study dietitian^]
- Resting blood pressure (BP) (mmHg) [measured after 5 minutes of seated rest by study dietitian^]
- Fasting blood glucose (mmol/L)\*

- Kidney function (Sodium, Potassium, Chloride, Bicarbonate, Urea, Creatinine, eGFR, Calcium, Corrected Calcium, Phosphate, Uric Acid)\*
- Liver function (Total Protein, Albumin, Alkaline Phosphatase, Total Bilirubin, Gamma GT, AST, ALT, Globulin, Magnesium, Creatine Kinase)\*
- Lipid studies (Cholesterol, HDL/LDL, Non-HDL Cholesterol, Triglycerides, LDL/HDL Ratio, Chol/HDL Ratio)\*
- Physical activity level [self-report using the International Physical Activity Questionnaire [31]]
- Dietary intake (total energy, digestible carbohydrate, dietary fibre, protein, total fat, saturated fat, monounsaturated fat, polyunsaturated fat as kJ/day and kcal/day or g/day) [derived from self-report 3-day weighed food record collected using Xyris *Easy Diet Diary* and analysed using Xyris *FoodWorks Professional Edition*]
- Diet satisfaction [self-report using a 6-item questionnaire [26]]

\*All biological samples will be collected and analysed by a NATA-Accredited Laboratory (Australian Clinical Labs) using standard procedures.

^Participants completing their clinic visits remotely will be asked to visit their nominated healthcare practitioner or local pharmacy to have anthropometric outcomes measured and recorded. Written instructions will be provided.

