## 5. PARTICIPATING SITES

This project will include both online (Telehealth) and in-person contact. Online visits will be conducted via Telehealth using Zoom video conferencing (<https://zoom.us>). Clinic visits will be conducted from a private clinic room at the Susan Wakil Health Building (The University of Sydney, [name]). There is opportunity for fully remote participation in this study, if required or preferred. In addition, this study provides opportunity for a member of participants' usual diabetes care team to be involved. Before entry into the study, participants will be required to nominate one member of their usual diabetes care team who is proficient in insulin management (i.e., an endocrinologist, a general practitioner or a diabetes educator). The nominated healthcare practitioner (HCP) will be made fully aware in writing of their patient's intention to participate in the study and details of the intervention. The HCP will be asked to confirm their ability and willingness to provide ongoing support (usual care) and medical oversight (specifically, management of insulin therapy) to their patient(s) throughout the duration of the intervention from their usual practice location or via Telehealth on an as-needed basis.

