#### **6.6.6 Outcome measurements (post-intervention)**

During the last week of the intervention period (week 16), participants will be required to have their outcomes measured seven days apart. All health outcome measurements will be collected following the same procedures outlined in the control period. See Table 1 and Figure 1 for a detailed schedule of what outcomes will be measured and when throughout the entire study.

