| Clinic visit 6
(end of week 16)                                               | 
 
Morning of clinic visit 6: Participants attend their nearest Australian Clinical Labs collection centre (fasted) to have biological samples taken. Participants instructed to have a meal and drink fluids after blood draw and before their clinic visit.
 
Data collected (post-intervention outcomes): 
 
Return/upload CGM/FGM device/data
 
Return/upload insulin logbook
 
Return/upload diet record
 
Anthropometric measurements taken (weight, height, waist circumference and blood pressure)
 
Questionnaires completed (quality of life, physical activity, diet satisfaction)
 
 
 
End of intervention period – participants thanked for being involved in study and encouraged to follow up with usual healthcare team for all matters.
 
Provide letter with instructions for follow-up period (Attachment 14)
 
Provide pre-paid pathology request form (from iMedical) for follow-up HbA1c
 
Follow-up session scheduled and participants informed they will receive an email with instructions 2 weeks prior.
 
 |

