| Email reminder
(start of week 27) | 
 
• Participants reminded that they will need to visit an Australian Clinical Labs pathology collection centre ~3 days before their follow-up session.
 
• Brief outline for follow-up call provided.
 
                                                                                                                                                                                                                                                                                                                              |
| Follow-up session (end of week 28)   | 
Telehealth call (Zoom) with study dietitian.
 
 
• Data collected (post-control/pre-intervention outcomes): 
 
- HbA1c (collected via Australian Clinical Labs and iMedical)
 
- Total daily insulin use (24-hour)
 
- Diet recall (24-hour)
 
- Questionnaires completed (quality of life, diet satisfaction)
 
 
 
• End of study – participants thanked for being involved in study and reminded to follow up with usual healthcare team for all matters.
 
 |

Text message reminders will be sent to participants the day before each visit/session.

[figure not shown]

Figure 1. Overview of Contact Schedule for Participants

Abbreviations: CGM, continuous glucose monitor; T1D, type 1 diabetes; HCP, healthcare practitioner; Ax, assessment; req., required; inc., including; d, day; ACL, Australian Clinical Labs Pathology Collection Centre.

Clinic visits may be completed online via Zoom video Conferencing or in person at the Susan Wakil Health Building at the University of Sydney .

Table 2. Study Milestones

| Milestone | Description                                                                                | Time      | Date                           |
|-----------|--------------------------------------------------------------------------------------------|-----------|--------------------------------|
| #1        | Study starts & recruitment period begins                                                   | 0 months  | 21 st June 2021     |
| #2        | Recruitment period ends (unless 20 participants recruited prior)                           | 5 months  | 30 th November 2021 |

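### Height is re-measured at three visits, so BMI change carries avoidable error, and the protocol body does not keep each participant on one site and device for weight, waist and blood pressure

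*Protocol*

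**What the plan says.** Section 9.3 lists BMI, waist circumference and resting blood pressure as additional outcomes. By default the study dietitian takes them: for BMI, "height and weight measured using standard procedures by study dietitian"; for blood pressure, "measured after 5 minutes of seated rest by study dietitian". All three carry a footnote under which remote participants "will be asked to visit their nominated healthcare practitioner or local pharmacy to have anthropometric outcomes measured and recorded". The footnote adds that written instructions will be given; their content is not in the protocol.

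Section 5 offers the remote route to anyone: "There is opportunity for fully remote participation in this study, if required or preferred". The note to Figure 1 says "Clinic visits may be completed online via Zoom video Conferencing or in person at the Susan Wakil Health Building".

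Section 9 sets three time-points for these outcomes: before the control period, after it, and after the intervention. In Table 1 these are clinic visits 2, 4 and 6 (end of weeks 0, 4 and 16). The entry is the same at each: "Anthropometric measurements taken (weight, height, waist circumference and blood pressure". Height is therefore taken three times.

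On consistency, Section 6.6.6 says of the post-intervention visit: "All health outcome measurements will be collected following the same procedures outlined in the control period". The control-period text in Section 6.5 names no site, device or observer. Section 6.3 analyses each outcome as a within-group difference across time.

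**The concern.** Every result in this single-arm study is a change within a person. Anything that differs between a participant's visits, other than the diet, goes into that change, and no concurrent control group can reveal it.

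There are two separate sources. The first is written into Table 1 and can affect every participant. Adult height is effectively constant over 16 weeks, so a second and third reading add only error to BMI change. Section 9.3 lists BMI and not weight as the outcome, which makes this more than a matter of record keeping.

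The second is something the protocol allows but does not plan. A participant could be measured by the dietitian at one visit and at a pharmacy at another, or at two different pharmacies, on different scales and cuffs. That adds noise to changes in weight, waist and blood pressure. It adds bias only if the moves follow a time pattern, for example in person at week 0 and remote at week 16. The 4-week control period would not expose a move made after week 4.

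**Working it through.** The protocol gives no SD, precision target or power for BMI, weight, waist or blood pressure, so there is no figure of its own to reproduce. Its sample size (16, raised to 20 for dropout) concerns HbA1c and does not bear on this point. Device differences, SDs of change and switching shares below are assumptions.

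**Height error, no switching needed.** BMI = weight / height². Take BMI 27, unchanged weight, and a second height reading 1 cm higher.
- Height 1.70 m: weight = 27 × 1.70² = 78.03 kg. New BMI = 78.03 / 1.71² = 26.685. The shift is -0.315 kg/m2, equal to 0.315 × 1.70² = 0.91 kg.
- Height 1.60 m: shift -0.334 kg/m2, or 0.86 kg.
- Height 1.80 m: shift -0.298 kg/m2, or 0.96 kg.

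A 1 cm discrepancy is therefore worth about 0.3 kg/m2, or about 0.9-1.0 kg. At 0.5 cm the shift is 0.15-0.17 kg/m2; at 2 cm it is 0.59-0.66 kg/m2.

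As random noise with SD h cm per reading at 170 cm, the SD added to BMI change is 2 × 27 × √2 × h / 170. This gives 0.22 kg/m2 for h = 0.5 and 0.45 kg/m2 for h = 1.0. With one height reused, it is zero.

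**Site or device switch.** Let s be the SD of one device's offset and p the share of participants who switch between two unrelated devices. A switch adds 2s² to that person's variance of change, so across the group

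inflation of the SD of change = √(SD² + p × 2s²) / SD.

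| Measure | Assumed SD of change | Assumed s | p = 10% | p = 25% |
|---|---|---|---|---|
| Weight | 2 kg | 0.5 kg | √4.05 / 2 = 1.006 | √4.125 / 2 = 1.016 |
| Weight | 2 kg | 1.0 kg | √4.2 / 2 = 1.025 | √4.5 / 2 = 1.061 |
| Blood pressure | 8 mmHg | 3 mmHg | √65.8 / 8 = 1.014 | √68.5 / 8 = 1.035 |
| Blood pressure | 8 mmHg | 5 mmHg | √69 / 8 = 1.038 | √76.5 / 8 = 1.093 |

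The inflation is about 0.6-6% for weight and 1.4-9% for blood pressure. No comparable range was worked out for waist.

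**Bias.** If the switchers' new devices all read 1 unit off in the same direction, the mean change shifts by p × 1, which is 0.10 to 0.25 units at 10-25% switching. If offsets are unrelated to time, the expected shift is zero.

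**The case against.** The strongest reply is that switching is inferred. The footnote in Section 9.3 and the wording of Sections 5 and 7.3.6 describe remote participation mainly as a property of the participant, not of the visit. Someone who is always in person, or always at the same pharmacy, changes nothing. Section 5 also has each participant nominate one practitioner, so that route points to a single place. Section 9.3 fixes the waist landmark and the seated rest before blood pressure, Section 6.6.6 asks for the same procedures, and the unseen instructions may ask for the same site and device. All of this stands. What remains is that the pharmacy route names no particular pharmacy, that the note to Figure 1 leaves mode open, and that the same procedure on another scale is still another scale.

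A reader might infer that participants will move between sites, or that the SD of change will rise by 6-22% for weight and 13-33% for blood pressure. The documents support neither. No passage plans a switch or says how often one would occur, and those percentages apply only to a participant who does switch, or to the group if everyone did. A reader might also infer a distorted blood pressure signal from the raised sodium advice. Section 7.3.3 follows the sodium risk through serum sodium and symptoms, not blood pressure.

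On height, it is fair to say that Table 1 does not state which reading enters BMI, and an analysis plan could choose the first. Weight is also recorded at each visit, so weight change itself is free of height error. But the repeated measurement is an explicit instruction, and Sections 9 and 9.3 together read most naturally as a fresh height for each BMI.

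**Conclusion.** The point holds in two parts of unequal firmness. Re-measuring height is a stated procedure that adds avoidable error to BMI change: about 0.3 kg/m2 for each centimetre of discrepancy, assuming BMI 27 and heights of 1.60-1.80 m. The gap on site and device is an omission from the protocol body, possibly filled by instructions that are not shown. Its effect is modest under the assumed device differences and 10-25% switching. Bias would require switching, or device offset, to be related to time, and nothing in the protocol indicates that.

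This is not a contradiction and does not threaten the trial's main conclusions. BMI, waist and blood pressure are additional outcomes; HbA1c and all secondary outcomes are untouched. It is a worthwhile minor improvement.

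**What to change.** - **Table 1:** delete height from clinic visits 4 and 6. State in Section 9.3 that the height from clinic visit 2 is used for every BMI. This saves two measurements per participant.
- **Section 9.3 footnote:** state that each participant uses the same site and device for weight, waist and blood pressure at weeks 0, 4 and 16 where possible, and repeat this in the written instructions for remote participants.
- **Data collection (Section 10.1):** record site and device at each of the three visits, so that any switch can be identified and results checked in participants whose site did not change.

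The cost is a few lines of protocol text, an edit to the instruction sheet and two short data fields. Participants lose a little freedom to change visit mode for these measurements. No visit is added.
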